### Secondary endpoint

1.3

The first secondary outcome to evaluate is the sensitivity/specificity of the pH test compared to the current Gold Standard (chest X-ray), also in consideration of clinical variables such as: food intake (time calculated in minutes from the last food intake, guaranteeing a minimum time to perform the test of at least 1 h) and taking drugs that affect gastric pH (proton pump inhibitors and antacids). Secondly, to evaluate the tolerance of the different NGT models used through pain monitoring (evaluated through the NRS scale at 24-48-72 h after placement and where an NRS score greater than ≥3 will be considered as a threshold value to identify poor tolerance). Thirdly, to evaluate the starting time of nutritional therapy from the request for placement of the NGT by the attending physician (calculated in minutes). Lastly, to evaluate possible complications associated with the positioning of the NGT and arising during the hospitalization period, such as: 1) mispositioning of the NGT (assessed with Chest X-ray); 2) tracheobronchial aspiration; 3) aspiration pneumonia 4) lesions of the oesophageal mucosa and of the upper airways (for points 2,3,4 evaluations by clinical examination, blood tests and instrumental tests requested by the attending physician).

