### Study procedures

2.2

Participants will be enrolled in three study arms, assigned according to the defined randomization criterion, to evaluate three different NGT models along with the use of an electronic pH meter. The first NGT is the *NUTRICIA FLOCARE PUR TUBE CH14 double lumen*, which features an additional lumen to the nutritional lumen specifically for pH aspiration. The other two NGTs are the *INNOVAMEDICA single lumen CH10 AVANOS_ST CH10* and the *INNOVAMEDICA single lumen CH12 AVANOS_ST CH12*, which have a single lumen. In all three study arms, the determination of the correct positioning (primary outcome) will take place through the monitoring of the gastric pH (gastric aspirate 5 ml; pH value ≤ 5.5)^46^ through the use of an electronic pH meter (pH Strips & Reader Innovamedica model pH X-act) which will be compared with the CXR (current gold standard). The comparison with the CXR will allow to evaluate the sensitivity and specificity of the pH test. An important aspect of the study is the evaluation of the time efficiency in starting nutritional therapy. This is measured in minutes and aims to determine if the pH test can reduce the time taken for NGT positioning evaluation compared to the current 1440 min required for chest X-ray assessments. The time frame is obtained from the evaluation of the service at IRCSS Humanitas Research Hospital. Furthermore, Patient tolerance to the NGT will be assessed at 24, 48 72 h post-placement using the NRS scale. This will help identify pain levels and characteristics, to evaluate whether different NGT calibers (CH) affect patient tolerance. Throughout the entire period of hospitalization of the patient, complications associated with the positioning of the NGT will be recorded. These include mispositioning of the NGT (assessed by chest x-ray); tracheobronchial aspiration; aspiration pneumonia; lesions of the oesophageal mucosa and upper airways (assessed by clinical examination and instrumental tests requested by the attending physicians). During the post-clinical phase, an economic analysis will be conducted to evaluate potential cost savings from using the pH test for correct NGT positioning, with respect to X-ray use. This includes analysing costs of auxiliary personnel (based on transport times to radiology, calculated as Euro/hour), professional fees for performing chest Xrays, and the cost of the Xrays themselves. A graphical representation of the study procedures is depicted in Fig. 1.

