#### Determination of sample size

2.5.1

Under the hypothesis that with standard method only 42 % of catheter positioning of the NGT allow the measurement of the pH of the gastric aspirate, we want to demonstrate, with a power of 80 % and a type I error of 5 % that the 3 studied NGT allow measurement of pH in at least 62 % of positioning. Therefore, the study need 47 patients in each arm. These numbers were gathered from the current data available at IRCCS Humanitas Research Hospital. This sample size also allows us to see a difference in discomfort between the three study groups as the difference in NGT calibre could be tolerated differently (NRS scale). Following this analysis, a total of 150 patients, subdivided into 50 patients per branch, have to be included in the study.

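### The sample size section claims adequacy for discomfort without any discomfort calculation, the NRS cut-off contradicts itself at a score of 3, and only CH10 against CH12 isolates calibre

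*Protocol article*

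**What the plan says.** Section 2.5.1 (Determination of sample size) builds the sample size on pH measurability. Its premise is that "with standard method only 42 % of catheter positioning of the NGT allow the measurement of the pH of the gastric aspirate", and it aims to show that "the 3 studied NGT allow measurement of pH in at least 62 % of positioning", at 80% power and a 5% type I error. It concludes: "Therefore, the study need 47 patients in each arm". It then adds: "This sample size also allows us to see a difference in discomfort between the three study groups", giving as the reason that tubes of different calibre may be tolerated differently. The planned number is 50 per arm, 150 in total.

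Three other sections bear on this claim:

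- Section 1.3 (Secondary endpoint) has NRS pain recorded at 24, 48 and 72 h, "where an NRS score greater than ≥3 will be considered as a threshold value to identify poor tolerance".
- Section 2.2 (Study procedures) says the NRS assessment is meant "to evaluate whether different NGT calibers (CH) affect patient tolerance". The three devices are a CH14 double-lumen tube of one product line, "which features an additional lumen to the nutritional lumen specifically for pH aspiration", and CH10 and CH12 single-lumen tubes that share another product line.
- Section 2.5.3 (Statistical analysis) plans chi-square tests for categorical variables and ANOVA or Kruskal-Wallis for continuous ones, across the three groups.

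**The concern.** The discomfort sentence is a positive claim of adequacy. No NRS difference, SD, poor-tolerance rate, time point or power stands behind it, and the calculation just before it addresses another question. Section 3 of the article says the choice among the tubes will also weigh tolerability. A reader who trusts the sentence could take a non-significant comparison as evidence that the tubes are equally tolerated, when the trial had little chance of showing a modest difference.

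Two further defects affect the same comparison. The cut-off joins a strict and a non-strict inequality, so a patient scoring exactly 3 is a poor-tolerance case under one reading and not under the other. And because sections 2.2 and 2.5.1 frame the question as one of calibre, a difference driven by the CH14 arm could be credited to calibre when the second lumen or the product may explain it.

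**Working it through.** **1. The plan's own figure.** Inputs from section 2.5.1: p0 = 0.42, p1 = 0.62, alpha = 0.05, power = 0.80. Sidedness is not stated. Testing one arm against a fixed 42%, two-sided, by the normal approximation:

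n = [(1.96 × √(0.42 × 0.58) + 0.842 × √(0.62 × 0.38)) / 0.20]² = [(0.967 + 0.409) / 0.20]² = 47.3

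This matches the stated 47. Other constructions do not: one-sample one-sided gives 37.2, and a two-arm comparison of 42% with 62% gives 97 per arm two-sided or 77 one-sided. The stated size is therefore a single-arm calculation and says nothing on its own about differences between arms.

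**2. What 50 per arm can detect for poor tolerance.** The protocol gives no rate, so base rates of 10% to 50% are assumed. For the three-group chi-square (2 df) the noncentrality is λ = n × Σ(p_i − p̄)² / [p̄(1 − p̄)] with n = 50, and 80% power needs λ of about 9.63.

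| Assumed base rate | Gap needed, one arm higher | Gap needed, evenly spaced |
|---|---|---|
| 10% | 20 points | 26 points |
| 20% | 24 points | 30 points |
| 30% | 26 points | 31 points |
| 40% | 27 points | 31 points |
| 50% | 26 points | 30 points |

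Power from an assumed 20% base:

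| Best-to-worst gap | One arm higher | Evenly spaced |
|---|---|---|
| 10 points | 20/20/30%: λ = 1.86, power 21% | 20/25/30%: λ = 1.33, power 16% |
| 20 points | 20/20/40%: λ = 6.82, power 64% | 20/30/40%: λ = 4.76, power 48% |

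**3. What 50 per arm can detect for the NRS score.** One-way ANOVA with three groups of 50 (noncentral F) reaches 80% power at f = 0.256.

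- One arm differs: gap = f × 3/√2 = 0.54 SD.
- Evenly spaced: gap = f × √6 = 0.63 SD.
- At an assumed SD of 2 these are 1.1 and 1.3 NRS points.

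**4. The CH10 against CH12 contrast alone.** Unadjusted, with 50 per arm, the detectable difference is (1.96 + 0.842) × √(2/50) = 0.56 SD, or 1.12 points at an assumed SD of 2. On the dichotomy it is 20% against 46%.

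**5. Cut-off.** On the integer NRS, the strict reading puts poor tolerance at 4 and above; the non-strict reading puts it at 3 and above. They disagree for every patient who scores 3.

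**6. Attribution to calibre.**

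| Contrast | Calibre differs | Lumen number differs | Product line differs |
|---|---|---|---|
| CH10 v CH12 | yes | no | no |
| CH14 v CH10 | yes | yes | yes |
| CH14 v CH12 | yes | yes | yes |

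**The case against.** The strongest defence is that discomfort is a secondary outcome, that section 2.5.3 speaks only of exploring group differences, and that the sentence refers to the NRS scale rather than to the dichotomy. On the score, 0.54 to 0.63 SD is a moderate effect. This stands. A reader might infer from the percentage-point figures that the trial can see only very large differences; that fits the dichotomised endpoint at best and does not describe the score. Evenly spaced arms are also the least favourable pattern for a given best-to-worst gap, so no single detectable figure holds in general.

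Three other stronger readings are not supported:

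- That the sample size is miscalculated. The 47 reproduces, and no discomfort figure is stated that could be wrong.
- That separate tests will be run at 24, 48 and 72 h. The article gives assessment times but does not say how they are combined; that may be left to a fuller document.
- That calibre cannot be studied at all. CH10 and CH12 share lumen type and product line. Section 1.3 also frames tolerance as a comparison of tube models, which the three-arm test does address.

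It is also fair to say that no section commits the authors to reading a null result as equal tolerance. That remains a risk created by the adequacy sentence, not a stated plan.

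None of this supplies a basis for the sentence, resolves the two inequality signs, or lets a CH14 contrast isolate calibre.

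**Conclusion.** The point holds as three linked defects of statement. First, the adequacy claim for discomfort is unsupported: it rests on a one-sample calculation for another endpoint. The sensitivity that 50 per arm does provide is limited for the poor-tolerance rate and moderate for the NRS score, and a 10-point difference in the rate would usually be missed. These magnitudes depend on assumed base rates and an assumed SD, because the document gives neither, and on complete data in all 50 patients per arm. Second, the cut-off is contradictory for a score of 3. This needs no assumption. Third, calibre is confounded with lumen number and product line in both contrasts that involve CH14. The remaining clean contrast spans one step of 2 CH.

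**What to change.** - **Section 2.5.1:** delete the discomfort sentence. Alternatively, replace it with the detectable difference, naming the NRS measure, the pattern of arms and the assumed rate or SD, and call the discomfort comparison exploratory.
- **Section 1.3:** write the poor-tolerance cut-off with a single operator, settled before any data are seen.
- **Sections 2.2 and 2.5.1:** limit inference about calibre to CH10 against CH12, reported as a difference with a 95% CI, and describe any CH14 result as a device-level comparison.

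These are wording changes and one prespecified contrast, with no added patients or assessments. The cost is that the stated sensitivity for discomfort becomes less favourable, and that the calibre question rests on two arms instead of three.

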#### Analysis populations

2.5.2

All randomized patients will be evaluated as Intent-to-Treat (ITT) bases, so all randomized patients classified on the basis of the treatment arm they were randomized to. If any patients, for any reason switch to another group, also a per protocol (PP) analysis wil be performed, and the patients will be considered in the treatment arm they received. Patients with pH measurement will be considered as the measured population (MP).

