### Primary endpoint

1.2

Evaluate the correct positioning of the NGT for enteral nutrition assuming an aspiration of the gastric aspirate of at least 5 ml in order to be able to carry out the pH test using an electronic pH meter (measurement carried out at the first positioning of the NGT).

Ability of the pH test to identify incorrect positioning of the SNG as well as the result of the chest x-ray. Furthermore, in the event of a doubtful RX result or one that does not identify the correct positioning, the pH test is able to detect the incorrect positioning.

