#### Clinical investigation intervention

2.2.5

*Medical device.* This randomized clinical trial will include three study arms to which patients will be assigned according to the enrolment criteria set out in the research protocol. Each arm of the study will involve a different type of NGT. The types of NGTs are reported in section 1.1. These two NGTs have a single lumen and are made of specific materials that give greater performance. In all three study arms, the determination of the correct positioning (primary outcome) will take place through the monitoring of the gastric pH (gastric aspirate 5 ml; pH value ≤ 5.5) through the use of an electronic pH meter (pH Strips & Reader pH X-act) which will be compared with the chest X-ray (current gold standard).

*Labelling and supply.* All electro medical equipment (pH meter) for this study will be provided free of charge for testing purposes by the respective manufacturers/suppliers, while medical devices (NGTs) will be provided free of charge.

*Storage conditions.* The NGT devices can be kept in the common storage environments used for the principals. A total of two pH metres will be assigned to each ward. The management and storage of the device will be carried out by the analysis laboratory of the structure in which the trial is being performed.

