#### Discontinuation or modifications of the intervention

2.2.6

Interruption of treatment foreseen in case of impossibility to carry out the NGT positioning procedure.

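### The analysis that section 2.5.2 calls per protocol is an as-treated analysis: it reassigns switchers to the tube they received and excludes no departures

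*Protocol article*

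**What the plan says.** Section 2.5.2 (Analysis populations) of the protocol article names three populations.

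- **ITT:** "all randomized patients classified on the basis of the treatment arm they were randomized to".
- **Per protocol:** the trigger is "If any patients, for any reason switch to another group". The rule is then "also a per protocol (PP) analysis wil be performed, and the patients will be considered in the treatment arm they received". No list or type of departure to be excluded is attached to this population.
- **Measured population:** patients who have a pH measurement.

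Three other sections bear on how the second rule works.

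- Section 2.2.5 (Clinical investigation intervention) defines the arms by device: "Each arm of the study will involve a different type of NGT". The arm received is therefore the tube received.
- Section 1.2 (Primary endpoint) fixes the time of the outcome: "measurement carried out at the first positioning of the NGT".
- Section 2.2.6 (Discontinuation or modifications of the intervention) covers a tube that cannot be placed: "Interruption of treatment foreseen in case of impossibility to carry out the NGT positioning procedure".

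**The concern.** A per-protocol analysis keeps patients in their randomised arm and leaves out those who departed from the protocol in specified ways. An analysis that counts each patient under the treatment actually received is as-treated. Section 2.5.2 gives the first name to the second analysis.

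The label matters here because a switch can be tied to the outcome. The primary endpoint is whether enough aspirate is obtained for the pH test, and the tubes differ in calibre and lumen design. The trigger covers a switch for any reason, so it includes one made because the assigned tube could not be passed or did not aspirate. Under the written rule that patient leaves the arm in which the failure occurred and is counted in another arm.

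At stake is how the result is read. Readers would take a non-randomised comparison by tube received as a per-protocol check on the ITT result.

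**Working it through.** **1. Classify the rule.** Section 2.5.2 assigns switchers to the arm received, and section 2.2.5 makes the arm the tube type. The rule therefore reassigns patients by tube received and states no exclusion. That is as-treated.

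**2. The plan's own figure.** The point depends on no stated number, but section 2.5.1 supplies the reference rate (42%), the target rate (62%) and the arm size (47 needed, 50 planned). The 47 reproduces closely as a two-sided one-sample test of 62% against 42%:

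n = [1.960 × √(0.42 × 0.58) + 0.842 × √(0.62 × 0.38)]² / 0.20² = 47.3

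The choice of analysis population does not alter this figure.

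**3. Illustration.** From the documents: 50 patients per arm and the 62% target, so 31/50 successes. Assumed: two arms, A and B, both at 31/50 at first positioning with the assigned tube; m failures of tube A then switch to tube B; y of those m succeed with B, and that second result is the one counted.

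- ITT by first positioning: A = 31/50, B = 31/50, both 62.0%.
- Written rule: A = 31/(50 − m), B = (31 + y)/(50 + m).

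| m | Arm A | Arm B if none succeed (y = 0) | Arm B if all succeed (y = m) |
|---|---|---|---|
| 2 | 31/48 = 64.6% | 31/52 = 59.6% | 33/52 = 63.5% |
| 3 | 31/47 = 66.0% | 31/53 = 58.5% | 34/53 = 64.2% |
| 5 | 31/45 = 68.9% | 31/55 = 56.4% | 36/55 = 65.5% |
| 10 | 31/40 = 77.5% | 31/60 = 51.7% | 41/60 = 68.3% |

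Arm A always rises, because only failures leave it. Arm B rises only if y/m exceeds 62%. With five switches, two tubes of equal first-attempt performance differ by 68.9 − 65.5 = 3.4 to 68.9 − 56.4 = 12.5 points.

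**4. Would a conventional per-protocol set cure this?** Only in part. If the switchers are simply excluded, B returns to 31/50 = 62.0%, but with m = 3 A is still 31/47 = 66.0%. The inflation of A comes from removing failures, and both rules do that. Exclusion alone is therefore not enough: the outcome must also stay with the assigned tube.

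**The case against.** The strongest defence is that the harm rests on crossover that the documents do not describe. No section provides for trying another arm's tube after a failure. Section 2.2.6 foresees interruption when positioning is impossible. The current local practice described in the Introduction goes to chest X-ray when the aspiration and pH procedure is unsuccessful. A patient given the wrong tube at first insertion fits the trigger equally well and is not a tube failure. This stands: failure-driven switching is allowed by the wording but is not shown to be likely.

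A reader might also infer that section 2.5.2 contradicts section 1.2. It does not. Section 1.2 ties the outcome to first positioning and nothing in 2.5.2 cancels that. Read together, a second tube's result need not count at all. But 2.5.2 does not say how the two combine for a patient who switches, so a clarifying sentence is worthwhile.

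A reader might further infer a predictable bias between arms. Only the originating arm's direction is fixed, and only if the switches follow failure. The receiving arm can move either way.

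Finally, an article may leave the list of excluded deviations to the full protocol or the SAP, so its absence is no finding. That does not rescue the rule itself, which the article states and misnames.

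**Conclusion.** The point holds as one of definition and labelling, with a conditional effect on the numbers. Section 2.5.2 describes an as-treated analysis and calls it per protocol.

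If switches follow failure of the assigned tube and the rule is applied to the second tube's result, the originating arm's rate is inflated: by 4 points with three switches in 50 (62.0% to 66.0%) and by about 7 with five (62.0% to 68.9%). These sizes rest on the assumed equal rates of 62% and on assumed numbers of switches, since the documents report neither a rate nor reasons.

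It would be wrong to conclude that the trial's main result is compromised. ITT is correctly defined by randomised arm. The misnamed analysis is additional, has no stated confirmatory role, and is not run if nobody switches. The correction is worth making because it is nearly free and prevents a misreading.

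**What to change.** Amend section 2.5.2 in three respects.

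1. Rename the analysis by tube received 'as-treated' and label it exploratory.
2. If a per-protocol analysis is wanted, analyse patients only in their randomised arm. Exclude those given another arm's tube for reasons unrelated to failure of the assigned tube, and reassign nobody.
3. State that, consistent with section 1.2, the primary outcome in the ITT and per-protocol analyses is the result of the first positioning attempt with the assigned tube. A failure to place or aspirate, or a switch caused by such a failure, then stays a failure of the assigned arm. In the three-switch illustration, arm A remains 31/50 (62.0%) in both analyses.

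The third change needs the reason for each switch to be recorded, so that failure-driven switches can be told from misallocation. The cost is a few sentences, a little more analysis work and a slightly less favourable per-protocol rate. The sample size does not change.

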#### Statistical analysis

2.5.3

Continuous variables following a symmetric distribution will be presented with mean (SD), while skewed variables will be presented with median (IQR). Ordinal variables will be presented with median (IQR) and categorical variables will be presented as n (%). For primary endpoint, the percentage of catheter positioning allowing pH measurement will also be described with 95 % confidence interval. Differences among the three groups will be explored with chi square test for categorical variables, or one-way ANOVA or Kruskal Wallis test, for continuous variable, depending on their distribution shape. MP patients will also be analysed in order to explore the existence of a different pH threshold to identify the correct catheter positioning in case of use of antiacids-PPIs drugs. All analysis will be performed with Stata version 17 or superior. Statistical significance was set to p < 0.05.

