#### Methods for minimizing bias

2.2.4

The pH measurement of the gastric aspirate, as indicated by several authors, will be evaluated at least 1 h after food intake. If the patient is taking antacids or proton pump inhibitors (PPI), we hypothesize that the pH data may present possible alterations; in this regard we will record variables of interest, reporting everything in the CRF form, including the intake of antacids and/or PPI drugs, daily dosage, and time since the last intake of the drug at moment of pH measurement. We believe the latter evaluations are necessary as to date there are no clear guidelines, protocols or clinical studies that highlight how to deal with such possible clinical biases. Furthermore, the calibration of the instrument will be carried out daily following the instructions and kit which are provided by the manufacturer by a responsible and trained healthcare professional. Additionally, before the start of the study, a specific 2-h training session will be conducted to train healthcare professionals on the study procedures and the use of the pH meter. This course will be delivered by a specialist nurse, a nutritionist, and by the clinical quality and risk department of the hospital.

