#### Concomitant treatments

2.2.9

It is important to consider pharmaceuticals or medicines or supplements or foods that can alter gastric pH prior to the procedure.

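### If the tubes are compared on pH ≤ 5.5, the unadjusted chi-square test is valid but leaves recorded acid-suppressant use unused; the two readings of the primary outcome must also be reconciled.

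*Protocol article*

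**What the plan says.** All places are in the protocol article.

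**The outcome, first reading.** Section 2.2.5 (and section 2.2 in nearly the same terms) states that "the determination of the correct positioning (primary outcome) will take place through the monitoring of the gastric pH (gastric aspirate 5 ml; pH value ≤"; the cut-off given there is 5.5. The reading is taken with the electronic meter and compared with chest X-ray.

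**The outcome, second reading.** Section 1.2 frames the primary endpoint as correct positioning "assuming an aspiration of the gastric aspirate of at least 5 ml in order to be able to carry out the pH test". The sample size in section 2.5.1 starts from the premise that "with standard method only 42 % of catheter positioning of the NGT allow the measurement of the pH of the gastric aspirate" and aims to show that "the 3 studied NGT allow measurement of pH in at least 62 % of positioning". Section 2.5.3 follows suit: "For primary endpoint, the percentage of catheter positioning allowing pH measurement will also be described with 95 % confidence interval". No cut-off enters the sizing or this analysis.

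**The tube comparison.** Section 2.5.3: "Differences among the three groups will be explored with chi square test for categorical variables". No covariate or stratification is named. Section 2.2.2 describes sealed envelopes and names no stratification factor.

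**Acid-suppressing drugs.** They are not among the exclusions in section 2.2.1. Section 2.2.4, on minimising bias, records variables of interest, "including the intake of antacids and/or PPI drugs, daily dosage, and time since the last intake of the drug"; section 2.2.8 repeats this. Section 3 calls antacid or PPI therapy the main limitation, because a correctly placed tube may then read above 5.5. The drug data have two stated uses: the sensitivity/specificity endpoint (section 1.3) and a search for a different pH threshold in patients with a measurement (section 2.5.3). Section 2.2.9 casts the net wider: "It is important to consider pharmaceuticals or medicines or supplements or foods that can alter gastric pH prior to the procedure".

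**The concern.** If the tubes are compared on the share of patients with pH ≤ 5.5, the result depends on the tube and also on who takes a drug that raises gastric pH. The plan expects that effect and collects the data, but states a comparison that does not use them. Under either reading of the primary outcome, this share matters for the trial's purpose, since a reading above 5.5 is the article's own indication for X-ray. At stake are the power to tell the tubes apart, and how a trial should be read if one arm happens to contain many more drug users.

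A second, smaller matter is the drug variable. Sections 1.3 and 2.5.3 confine it to antacids and PPIs, whereas section 2.2.9 refers to anything that can alter gastric pH. A patient on another such agent could be counted as unexposed in the sensitivity/specificity and threshold analyses, which would blur the contrast those analyses are meant to show.

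**Working it through.** **Step 1. Which endpoint was sized?** Inputs from section 2.5.1: 42% against 62%, 80% power, 5% type I error, 47 per arm. For one proportion against a fixed 42%, two-sided, normal approximation:

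n = [1.96·√(0.42·0.58) + 0.8416·√(0.62·0.38)]² / 0.20² = (0.967 + 0.409)² / 0.04 = 47.3

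This matches the stated 47 to rounding. A two-sided two-sample comparison would need 97 per arm. So the trial is sized on each arm's measurability rate against 42%, and neither the cut-off nor drug use enters.

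**Step 2. Does the drug mechanism reach each reading?**

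- *pH measurable* (sections 1.2, 2.5.1, 2.5.3): a drug user with 5 ml of aspirate and a pH of, say, 6.5 counts as a success. The documents do not say that these drugs affect how much fluid can be drawn. The mechanism does not reach this endpoint.
- *pH ≤ 5.5* (sections 2.2, 2.2.5): the same patient counts as a failure. The mechanism applies.

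**Step 3. What does ignoring drug use cost on a pH ≤ 5.5 outcome?** The documents give neither the share of users nor the size of the drug effect, so both are assumptions: users 30%, 50% or 70%; success 80% in non-users and 60%, 40% or 20% in users. There were 200,000 simulated trials per scenario, three arms of 50, with drug use falling by chance. The unadjusted 3×2 chi-square was compared with a Cochran-Mantel-Haenszel (CMH) test stratified by drug use, both at 5% (critical value 5.991, 2 df). The gap is the number of users in the highest arm minus the lowest. Power is for one tube better by a log odds ratio of 1.0.

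| Users | Success in users | Chi-square error, overall | Trials with gap ≥ 10 | Chi-square error if gap ≥ 10 | CMH error if gap ≥ 10 | Power, chi-square | Power, CMH |
|---|---|---|---|---|---|---|---|
| 30% | 60% | 5.0% | 9.4% | 6.6% | 5.1% | 43.0% | 44.1% |
| 30% | 40% | 5.0% | 9.3% | 10.6% | 5.3% | 42.7% | 48.1% |
| 30% | 20% | 5.2% | 9.4% | 17.4% | 4.9% | 33.1% | 45.4% |
| 50% | 60% | 5.1% | 13.8% | 6.4% | 5.0% | 48.0% | 49.4% |
| 50% | 40% | 5.2% | 13.9% | 10.5% | 4.9% | 50.3% | 56.2% |
| 50% | 20% | 4.8% | 13.7% | 15.5% | 4.9% | 36.8% | 51.7% |
| 70% | 60% | 5.0% | 9.4% | 6.0% | 4.9% | 53.5% | 54.4% |
| 70% | 40% | 4.8% | 9.4% | 9.9% | 4.9% | 59.0% | 63.2% |
| 70% | 20% | 5.2% | 9.4% | 17.1% | 4.9% | 44.1% | 57.2% |

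Reading the table:

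- Overall error of the unadjusted test is 4.8% to 5.2%. The CMH test's overall error is 4.8% to 5.0%.
- In the 9% to 14% of trials with a gap of 10 or more users, the unadjusted test rejects in 6.0% to 17.4%. This is offset by 1.4% to 4.7% when the gap is below 5.
- The power gain runs from 54.4 − 53.5 = 0.9 points to 51.7 − 36.8 = 14.9 points, and is larger the stronger the drug effect.

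**The case against.** **Chance imbalance is not bias.** A reader might infer that an uneven spread of drug users would pass as a tube difference. Allocation is randomised, and such imbalance is part of the sampling variation that the 5% level already covers; the overall error rates above confirm it. Suppose the drug lowers success by 30 points (assumed). A 15-point imbalance in users then moves a tube difference by 0.15 × 0.30 = 4.5 points. With three identical tubes and 50 patients each, however, the highest and lowest arms are expected to differ by about 12 points anyway at a 42% or 62% success rate. The 4.5 points are a component of that variation and do not come on top of it. This objection stands. What is left is a gain in precision and a better reading of an imbalanced trial.

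**The sized endpoint is untouched.** This also stands, as step 2 shows. The point applies only where pH ≤ 5.5 is compared between tubes.

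**The drugs are not ignored.** They are recorded, enter two planned analyses and are disclosed as the main limitation. True, but neither planned use bears on the tube comparison.

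**Adjustment may sit in an SAP or full protocol not shown.** Silence alone would be no finding. Here, though, the article states a method for the group comparison, and a better one is available from data it already plans to collect.

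**The CRF is not shown.** Section 2.2.4 introduces the drugs with the word for a non-exhaustive list, so the CRF may already be broader. Misclassification is therefore possible but not shown.

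**Conclusion.** The point holds as a minor matter of efficiency and clarity. Two descriptions of the primary outcome stand side by side and must be reconciled. Where pH ≤ 5.5 is compared between tubes, the stated chi-square test is valid overall at about 5%, but it leaves out a recorded factor that the article itself expects to affect the reading. Under the assumed user shares and drug effects, stratifying gains about 1 to 15 points of power. It also holds the error near 5% in imbalanced trials, where the unadjusted test rejects in about 6% to 17%. The gain is near the lower end if the true drug effect is modest.

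The documents do not support the stronger readings that the planned comparison is biased, that imbalance creates a spurious tube effect, or that drug use threatens the measurability endpoint on which the trial is sized. The narrower drug variable is at odds with section 2.2.9, but whether any patient would be misclassified depends on a CRF that is not shown.

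**What to change.** 1. Reconcile sections 2.2 and 2.2.5 with sections 1.2, 2.5.1 and 2.5.3, so that one definition of the primary outcome holds throughout and any other is named as a separate outcome.
2. In section 2.5.3, for any comparison of pH ≤ 5.5 between tubes, keep the chi-square test as descriptive. Prespecify a Mantel-Haenszel (stratified) or logistic comparison adjusted for pre-placement acid-suppressant use (yes/no). Record that use for every randomised patient, including those from whom no aspirate is obtained, so that the adjusted analysis covers the intention-to-treat population.
3. Add no such adjustment to the measurability endpoint on the present rationale.
4. Align the drug variable in sections 1.3, 2.2.4, 2.2.8 and 2.5.3 with section 2.2.9, as any drug or supplement that can alter gastric pH. Use that same variable in the sensitivity/specificity and threshold analyses.

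Cost: a few sentences of analysis text, slightly more analysis work and one broader CRF item. No extra patients or visits. Fixing the adjustment now also avoids choosing it after an imbalance has been seen.
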